### Data collection and statistical analysis

The data collected will be stored in a database specially designed for this study using Access (Microsoft Office Access 2007). The data will be entered by a dedicated member of the project team, who will ensure the integrity and quality of the data. The statistical analyses will be carried out with the statistics program Stata v.14 [25].

We will perform a blind interim analysis when at least half of the patients have been recruited and followed for at least 1 year. We will stop the trial if the group difference in the main outcome is statistically significant at a significance boundary *p* < 0.0051. The final analysis with the whole trial population will be carried out at the end of the follow-up at a significance level of 0.04795.

For the univariate analysis of quantitative variables, we will check the normality of the data using the Kolmogorov–Smirnov test. Depending on the assumption of normality, the two arms will be compared using parametric tests (Student’s *t*-test) or nonparametric tests (Mann–Whitney *U* test). The associations of categorical variables with the two treatment groups will be assessed by chi-squared tests or Fisher exact tests, as appropriate.

The loss of renal function is evaluated by the diuresis in 24 h at 12 months after initiation of haemodialysis therapy, and it is dichotomized with a threshold of 100 mL in 24 h. A time-to-event analysis will estimate the probability of loss of kidney function in both treatment groups using the Kaplan–Meier method. Survival curves will be compared with log-rank tests. This survival analysis will be complemented with a proportional hazard model to estimate the hazard ratio of kidney function survival adjusted for any confounding factors to identify any imbalance in the baseline characteristics of the patients.

All analyses will be carried out in accordance with the intention-to-treat and per-protocol principles, assuming that in the worst case the losses to follow-up are a failure of the allocated treatment arm. In the final analyses, for the comparisons between the two treatment groups, the probability of rejecting the null hypothesis will be adjusted according to the O’Brien and Fleming method [26].

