### Outcomes

The main outcome is loss of kidney function, defined as urine volume output less than 100 mL in 24 h, 12 months after the initiation of haemodialysis therapy.

The secondary outcomes are: (1) erythropoietin dosage, (2) beta-2 microglobulin concentration, (3) hydration and nutritional status, (4) concentrations of uremic toxins, (5) dialysis dose, (6) number and duration of hospital admissions, (7) mortality and (8) quality of life.

In addition, cost-efficiency will be assessed by recording the cost of haemodialysis sessions and the monthly consumption of erythropoietin.

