### Trial design

This is a randomized prospective multi-centre open-label clinical trial. Randomization will be stratified in every recruitment centre, ensuring a 1:1 ratio between the two study groups in all centres. The trial compares the initiation of renal replacement therapy with two haemodialysis sessions per week to the conventional three sessions per week in patients with residual urea clearance rate KrU ≥ 2.5 mL/min/1.73 m^2^. As treatment masking is not feasible, treatment allocation is centralized for all participating hospitals, and performed by an agent external to the researchers. Once a participating centre has verified that a patient meets the inclusion criteria, the randomization centre will provide the treatment group allocation. The investigators will not know the randomization sequence. The two groups will be those beginning with two haemodialysis sessions per week (2HD) and those beginning with three haemodialysis sessions per week (3HD).

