### Participants

The participants are incident patients at five university hospitals in the Community of Madrid (Spain): H. U. Ramón y Cajal (coordinating centre), H. U. del Henares, H. U. La Paz, H. U. Príncipe de Asturias and H. U. Clínico San Carlos. The minimum follow-up period will be 1 year.

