### Assessments

The following will be assessed at the momento fo enrollment: age, sex, renal disease, Charlson comorbidity index, urine volume output in 24 h (mL), urea clearance (mL/min), creatinine clearance (mL/min).

The following will be assessed at the start of haemodialysis treatment (baseline) and every 2 months during a follow-up of at least 1 year: urine volume output in 24 h (mL), urea clearance (mL/min), creatinine clearance (mL/min), haemoglobin (g/dL), haematocrit (%), creatinine (mg/dL), urea (mg/dL), Na (mmol/L), K (mmol/L), albumin (g/dL), pre-albumin (mg/dL), calcium (mg/dL), phosphorus (mg/dL), parathyroid hormone (pg/mL), ferritin (ng/mL), beta-2 microglobulin (mg/L), brain-derived natriuretic peptide (pg/mL), C-reactive protein (mg/L), dose of dialysis (*Kt / V*), erythropoietin dosage (units per week per kg of weight), hydration, nutrition, hospital admissions, days of admission, causes of hospitalization and number of haemodialysis sessions.

The dose of dialysis is determined using the kinetic model of urea with the formulae modified from Gotch [22]. Dialysis *Kt* / *V* [3] is added to the residual renal function to give the total *Kt* / *V*:

Total *Kt* / *V* = dialysis *Kt* / *V* + (9.5 KrU) / *V* (for 2 haemodialysis sessions per week)

and

Total *Kt* / *V* = dialysis *Kt* / *V* + (5.5 KrU) / *V* (for 3 haemodialysis sessions per week),

where *V* is 58% of the dry weight (Watson formula) [23] and KrU is the residual urea clearance rate (mL/min).

Hydration and nutrition are measured by multi-frequency electrical bioimpedance (BCM®, Fresenius Medical Care). The following metrics are collected: overhydration (L), amount of extracellular water (L), amount of intracellular water (L), extracellular / intracellular ratio, body mass index (kg/m^2^), lean tissue index (kg/m^2^) and fat tissue index (kg/m^2^).

Quality of life will be assessed using the Kidney Disease Quality of Life Short Form at the start of haemodialysis treatment (baseline), at 6 months and at 12 months (close-out). This is a validated questionnaire for the haemodialysis population.

The schedule of enrolment, intervention and assessments is shown in Fig. 1.

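### The arms are compared by tests that name neither centre nor baseline renal function, and the covariates of the complementary Cox model are not fixed in advance: a loss of precision and an open choice, not an invalid primary test

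*Protocol article*

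**What the plan says.** Under Trial design, the article makes centre a design factor: "Randomization will be stratified in every recruitment centre, ensuring a 1:1 ratio between the two study groups in all centres". Participants lists five hospitals. Under Assessments, 24-h urine volume, urea clearance (KrU) and creatinine clearance are among the measurements taken "at the start of haemodialysis treatment (baseline) and every 2 months during a follow-up of at least 1 year". The primary endpoint is a threshold on one of these: "The main outcome is loss of kidney function, defined as urine volume output less than 100 mL in 24 h", at 12 months.

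Data collection and statistical analysis then sets out three comparisons:

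- Time to loss of function: "Survival curves will be compared with log-rank tests". No stratum is mentioned.
- Quantitative variables, under a univariate analysis: "Depending on the assumption of normality, the two arms will be compared using parametric tests", or else by Mann–Whitney, with a Kolmogorov–Smirnov test deciding between them. No baseline value, centre or repeated-visit term is mentioned.
- A Cox model that complements the survival curves, "adjusted for any confounding factors to identify any imbalance in the baseline characteristics of the patients". The abstract also refers to adjustment for confounders without naming any.

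**The concern.** Two things look wrong.

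First, the stated comparisons use neither the randomisation stratum nor baseline function. The endpoint is urine volume falling below 100 mL, and the Discussion treats 24-h diuresis as the proxy for residual function, so its starting level is a natural prognostic covariate. The Background itself names unequal renal function at the start of dialysis as a weakness of the earlier observational studies. With 44 patients per arm, ignoring such a covariate gives away precision that costs nothing to keep.

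Second, the Cox sentence fixes no covariate and links adjustment to baseline imbalance. Under randomisation, imbalance is chance. A covariate earns its place by prognostic strength, judged before outcomes are seen. If the list is settled afterwards, the adjusted hazard ratio depends on who chose it and when, which matters more in an open-label trial.

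**Working it through.** **1. The protocol's own figure.** Sample size gives mean declines of 0.18 and 0.33 mL/min/month, SD 0.25, two-sided alpha 0.05 and 80% power. (Both declines carry the same arm label; the difference is 0.15 either way.)

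n per arm = 2 × (1.960 + 0.842)² × 0.25² / 0.15² = 43.6, so 44. This reproduces the stated 44. Power at 44 = Φ(0.15 / (0.25 × √(2/44)) − 1.960) = Φ(2.814 − 1.960) = 80.4%. At the final-analysis level of 0.04795 it is 79.9%.

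**2. Adjusting that comparison for a baseline covariate.** Residual SD = 0.25 × √(1 − ρ²), where ρ is the correlation between covariate and outcome. The article gives no ρ, so a range is shown.

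| ρ (assumed) | Residual SD | Power at 44 per arm | n per arm for 80% |
|---|---|---|---|
| 0 | 0.250 | 80.4% | 44 |
| 0.2 | 0.245 | 81.9% | 42 |
| 0.3 | 0.238 | 83.9% | 40 |
| 0.5 | 0.217 | 90.1% | 33 |

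**3. Survival comparison, simulated.** All inputs except the total of 88, the five centres and the 12 months are assumptions: centre sizes 28, 20, 16, 14 and 10, balanced 1:1 within centre; exponential event times with hazard 0.06 per month in the reference arm; hazard ratio 0.45; no dropout; 2,000 runs per setting (Monte Carlo standard error about 1 point for power and 0.5 for type I error). The adjusted Cox model contained treatment and the baseline covariate, but not centre.

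| Centre SD (log hazard) | Baseline log HR per SD | Unstratified log-rank | Centre-stratified log-rank | Baseline-adjusted Cox | Type I error, unstratified log-rank |
|---|---|---|---|---|---|
| 0 | 0 | 63.3% | 62.3% | 61.6% | 5.4% |
| 0.3 | 0.5 | 57.6% | 58.0% | 61.4% | 5.2% |
| 0.5 | 0.5 | 58.4% | 60.6% | 61.0% | 4.2% |
| 0.5 | 1.0 | 45.1% | 46.4% | 60.0% | 4.7% |

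Where a centre effect exists, stratifying adds 0.4 to 2.2 points; where there is none, it costs about 1, which is within simulation error. Baseline adjustment adds about 3 to 4 points at a moderate prognostic effect and about 15 at a strong one. Type I error without strata stays at 4.2% to 5.4%.

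**4. Choosing covariates by imbalance, simulated.** Linear outcome, 44 per arm, standardised difference 0.15/0.25 = 0.6, three candidate covariates of which one is prognostic (ρ = 0.5), 2,000 runs.

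| Rule | Power | Rejection under the null |
|---|---|---|
| No adjustment | 80.3% | 5.3% |
| Prespecified prognostic covariate | 89.1% | 5.0% |
| Only covariates with significant imbalance | 81.3% | 4.2% |
| Most favourable covariate set | 91.3% | 8.4% |

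An imbalance rule followed strictly is safe but recovers almost none of the gain. The 8.4% is the limit if the choice is left wholly free.

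**5. Quantitative outcomes.** With equal variances at baseline and follow-up, the variance relative to a raw follow-up value is 1 − ρ² for ANCOVA and 2(1 − ρ) for change from baseline.

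- ρ = 0.5: ANCOVA 0.75, change 1.00. Equivalent n = 44/0.75 = 59 against either.
- ρ = 0.7: ANCOVA 0.51, change 0.60. Equivalent n = 44/0.51 = 86 against raw values, but 44/(0.51/0.60) = 52 against change.

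**The case against.** The strongest reply is that silence is being read as a decision. The article says log-rank; it does not say unstratified. Strata, covariate lists and repeated-measures models are often left to an analysis plan, which is not shown. That stands in part: nobody can say the log-rank will be run without strata, and absence of detail alone would be no point. But the article does more than omit. It names a test for quantitative variables, a pre-test to choose it, and a basis for Cox adjustment. Those stated choices can be improved.

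Next, the Cox sentence is garbled and concerns only a complementary model. Both are true. Selection by imbalance is the apparent meaning, not an explicit rule, and the log-rank does not depend on it. Still, no reading of the sentence fixes a covariate in advance.

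Third, the t and Mann–Whitney tests are called univariate and may not be the only analyses. They might be applied to slopes or changes, which already use the baseline value; the sample-size comparison is itself of monthly decline. This stands, so it cannot be said that baseline and repeated visits will be discarded.

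Fourth, the centre effect is small and the sizes rest on assumed inputs. Both are conceded.

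**Conclusion.** The point holds as one of efficiency and prespecification. The stated methods leave precision unused and leave the adjusted hazard ratio open to post hoc choice. On the protocol's own comparison of means, the unused gain is about 1.5 points of power at ρ = 0.2, 3.5 at 0.3 and 10 at 0.5. Centre contributes about 0 to 2 points in the survival simulation. The document supplies neither a correlation nor a centre effect, so these are ranges, not estimates for this trial.

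Stronger conclusions that a reader might infer are not supported:

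- That the primary test is biased or has inflated error. The simulated type I error does not show this.
- That the trial forgoes the equivalent of 59 to 86 patients per arm. That whole range applies only against raw follow-up values, at ρ of 0.5 to 0.7. Against change from baseline at 0.7 the figure is 52.
- That the Cox gains would reach the primary test once it is stratified by centre. They would not, because a centre-stratified log-rank still ignores baseline function.
- That baseline urine volume and KrU are the strongest predictors of the endpoint, or that the simulated powers show the trial to be short of power. The document ranks no predictors, and those powers follow from an assumed hazard ratio and event rate.

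**What to change.** - Fix the Cox model in advance: treatment, baseline 24-h urine volume and baseline KrU, with centre as a stratum, or as a covariate if strata are sparse. Name its treatment effect as the main adjusted estimate.
- Decide which test is primary. If the gain from baseline adjustment is wanted there, the treatment test from this Cox model must be the primary test.
- Stratify the log-rank by centre, so that it matches the randomisation.
- Delete the wording that links adjustment to imbalance.
- For quantitative outcomes, replace the normality pre-test and the choice it drives with ANCOVA on the baseline value, or a linear mixed model on the 2-monthly values with baseline, centre, visit and treatment-by-visit terms. Log-transform skewed variables.

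This should be settled before the interim comparison. The data are already scheduled, so the cost is revised wording and slightly more analysis work. Some centre strata may be sparse with 88 patients in five hospitals. The adjusted hazard ratio is conditional on baseline and need not equal the unadjusted one, so reports should say which is given.

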### Withdrawal criteria

Patients will be withdrawn from the study if they receive a renal transplant, die***,*** recover renal function or transfer to another facility or if they withdraw their informed consent.

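### The rule that scores losses to follow-up as failures does not say which exits it covers, and applying it to both arms is not a worst case

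*Protocol article*

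**What the plan says.** Three sections of the protocol article bear on this.

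- **Outcomes.** The definition reads: "The main outcome is loss of kidney function, defined as urine volume output less than 100 mL in 24 h, 12 months after the initiation" (that is, the start of dialysis). Mortality is listed separately, as a secondary outcome. Neither transplant nor recovery is part of the main outcome.
- **Withdrawal criteria.** The list opens with transplant: "Patients will be withdrawn from the study if they receive a renal transplant". Death is a further ground, and the remaining ones are given as: "recover renal function or transfer to another facility or if they withdraw their informed consent".
- **Data collection and statistical analysis.** The method is named first: "A time-to-event analysis will estimate the probability of loss of kidney function in both treatment groups using the Kaplan–Meier method". Log-rank tests and a proportional hazards model are added to it. The analysis principles come next: "All analyses will be carried out in accordance with the intention-to-treat and per-protocol principles". To these the section attaches its rule for losses: "assuming that in the worst case the losses to follow-up are a failure of the allocated treatment arm".

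The article does not say whether the listed withdrawals are losses to follow-up, and it does not exclude them. It gives no other rule for patients who leave before 12 months.

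**The concern.** The five exits carry quite different information about the outcome. Recovery of renal function is its opposite. Death and transplant prevent anuria from being observed on dialysis. Transfer and withdrawn consent leave the patient's status unknown. One rule that turns exits into failures changes the target from anuria to a mixture of anuria and leaving the trial.

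The rule also governs the result that matters most. The interim boundary (p < 0.0051) and the final level (0.04795) apply to the main outcome. The Limitations section defends the open-label design on the ground that anuria is quantitative and objective. That defence weakens for any event imputed from an exit, because patients and clinicians know the arm when an exit is decided.

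**Working it through.** **The plan's own figure.** The sample size rests on a difference in mean decline of 0.33 − 0.18 = 0.15 mL/min/month with SD 0.25 (both rates are printed against the 2HD group, but only the difference enters). By the normal approximation, n = 2 × (1.960 + 0.842)² × 0.25² / 0.15² = 43.6, so 44 per group, with power 80.4%. The stated figure reproduces. The rule for losses plays no part in it, and it supplies neither an anuria rate nor a loss rate.

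**Inputs for the check.**

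- From the article: 44 per arm and a final two-sided level of 0.04795.
- Assumed: the 12-month anuria risk *p* and the share lost *w* in each arm. Losses are taken as unrelated to anuria.
- Test: the uncorrected chi-squared test on the 12-month proportions, with exact binomial power. This stands in for the log-rank comparison.

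**Formula.** If every loss counts as a failure, the observed risk in an arm is q = w + (1 − w)p.

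**Equal losses.** The difference becomes q₃ − q₂ = (1 − w)(p₃ − p₂), so it shrinks by the factor (1 − w). With p₂ = 0.181, p₃ = 0.36 and w = 0.20:

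- 2HD: 0.20 + 0.80 × 0.181 = 0.345
- 3HD: 0.20 + 0.80 × 0.36 = 0.488
- The risk ratio moves from 0.50 to 0.71, and the risk difference from 0.179 to 0.143.

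| Losses in each arm | Power, losses = failure | Power, losses left out |
|---|---|---|
| 0% | 47% | 47% |
| 5% | 41% | 46% |
| 10% | 36% | 44% |
| 20% | 26% | 39% |

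The fair comparison is across a row. At 20% losses the fall from 47% to 39% is lost information that no coding rule restores. The further fall from 39% to 26%, about 13 points, is due to the rule.

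**Unequal losses, no true effect.** With the same *p* in both arms, q₃ − q₂ = (w₃ − w₂)(1 − p). With p = 0.25:

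| Losses, one arm vs the other | Spurious difference | False-positive rate |
|---|---|---|
| 5% vs 10% | 0.05 × 0.75 = 0.0375 | about 7% |
| 10% vs 20% | 0.10 × 0.75 = 0.075 | 11% |
| 5% vs 20% | 0.15 × 0.75 = 0.1125 | 20% |

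The arm with fewer losses looks better, whichever arm that is.

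**Unequal losses, true effect.** Take p₂ = 0.181 and p₃ = 0.36 again (true difference 0.179).

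- Losses of 20% in 2HD and 10% in 3HD: 0.345 vs 0.424, a difference of 0.079, power 12%.
- The reverse, 10% in 2HD and 20% in 3HD: 0.263 vs 0.488, a difference of 0.225, larger than the truth.

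**Is it a worst case?** The hypothesis is that 2HD does better. The least favourable coding for that hypothesis fails losses in 2HD and leaves losses in 3HD event-free. Failing losses in both arms is a different rule, and as the last example shows it can even exaggerate the benefit.

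**The case against.** The strongest reply is that the article never calls recovery, transplant or death a loss to follow-up. In ordinary use that term means status unknown, and for these three exits the status is known. On that reading the rule reaches only some transfers and withdrawals of consent. This stands: a reader might infer that the plan scores recovered patients as failures, but the text permits that reading without stating it. What remains is that the terms are not reconciled, and that the arithmetic above applies to the narrow reading too, with a smaller *w*.

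Second, the worst-case qualifier may mean a sensitivity scenario and not the primary coding. That is possible, but the sentence is attached to all analyses and no other primary coding is given.

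Third, a reader might infer that the rule contradicts the Kaplan–Meier analysis. It does not. A failure can be entered as an event at the exit date, and the article states no censoring rule that this would breach. The curve then estimates anuria or loss to follow-up, where the article promises "A time-to-event analysis will estimate the probability of loss of kidney function in both treatment groups".

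Fourth, censoring dates and competing-event methods commonly sit in an analysis plan that is not shown. Their absence alone would be no finding. The point here is a rule that the article does state.

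Fifth, nothing in the article shows that losses will differ by arm, or in which direction. This also stands: a tilt towards 2HD is one possibility and no more, and mild imbalance does limited harm. Finally, counting missing as failure in both arms is a recognised convention, and attenuates the effect when losses are balanced. Balance cannot be assumed in an open-label trial.

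**Conclusion.** The point holds as a badly fixed rule. The article's only instruction for patients without a 12-month urine volume leaves open which exits it covers and whether it is the primary coding. On its broad reading it conflicts with the definition of the main outcome. On either reading it is not a worst case. At 20% losses per arm it costs about 13 points of power beyond the loss of data itself. With no true effect, the false-positive rate runs from about 7% under mild imbalance to 20% for losses of 5% versus 20%. Every anuria and loss rate behind these figures is assumed, losses are taken as unrelated to anuria, and the direction of any bias cannot be known in advance. Left as it is, the choice between event and censoring could be made after open-label data have been seen.

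**What to change.** Reconcile the Outcomes, Withdrawal criteria and statistical analysis sections before any comparison by arm is run. For the primary time-to-event analysis, state that:

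- recovery of renal function is not an event;
- death and transplant are competing events, with cause-specific log-rank and Cox comparisons and cumulative incidence curves shown;
- transfers and withdrawn consent are censored at the last urine collection.

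Other coherent choices exist, such as a composite declared as the main outcome. What matters is that each exit is assigned in advance. Keep the coding of all losses as failures only as a sensitivity analysis, alongside a true worst case that fails losses in the 2HD arm only.

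The cost is revised wording and a little more programming, since the withdrawal reasons are already distinguished. The price in assumptions is that censoring for transfer and withdrawn consent is non-informative, which the two sensitivity analyses probe.
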